# Protocol and Ethical Review Application Form

Submission Date: January 10, 2014

To:

The Chairperson of the Clinical Ethics Committee of Labor Health and Welfare Organization,  
Ehime Rosai Hospital

Applicant, Affiliation:

[name]

Department of Gastroenterology and Neurology, Kagawa University, [name]

Department of Gastroenterological Surgery, Ehime Rosai Hospital, [name]

1. The name of the clinical study

Unavoidable human error in tumor sizing during attachment of resected specimens after  
endoscopic resection: a randomized prospective study

2. The manager of the study, Affiliation

[name]

Department of Gastroenterology and Neurology, Kagawa University, [name]

Department of Gastroenterological Surgery, Ehime Rosai Hospital, [name]

3. The collaborator and contributor of the study, Affiliation

[name]

Department of Gastroenterological Surgery, Ehime Rosai Hospital, [name]

[name], [name], [name], [name]

Department of Gastroenterology and Neurology, Kagawa University, [name]

4. Aim

Objective evaluation of resected specimens and tumor size is critical because the tumor diameter after endoscopic submucosal dissection (ESD) affects therapeutic strategies. In this study, we investigated whether the true tumor diameter of gastrointestinal cancer specimens measured by flexible endoscopy is subjective by testing if the specimen is correctly attached to a specimen board after ESD resection and whether the size differs depending on the endoscopist who attached the specimen.

#### 5. Subjects of this research and study

Patients who are diagnosed with early gastric cancer satisfied expanded-indication guideline for ESD of the Japan Gastric Cancer Association (JGCA). JGCA defined the expanded-indication inclusion criteria of ESD as follows: In differentiated gastric cancers, intramucosal carcinoma has no size restriction, whereas intramucosal carcinomas accompanied by ulcer scarring and SM1 carcinomas (500 $\mu$ m from the muscularis mucosae) should be <30 mm. In undifferentiated carcinomas, intramucosal carcinomas should be <20 mm. Included patients provided consent after receiving oral and written explanations of the study. The exclusion criterion was being diagnosed with a lesion with off-label indications for endoscopic resection before ESD according to the JGCA guidelines.

In this study, to improve patient outcomes, we investigated whether the true tumor diameters of gastrointestinal cancer specimens measured by flexible endoscopy are subjective by testing if the specimen is correctly attached to a specimen board after ESD resection and whether the size differs depending on the endoscopist who attached the specimen.

#### 7. Implementation plan

From among ten endoscopists, the two endoscopists engaged in the ESD were excluded. Three endoscopists were randomly selected before every ESD by the envelope method from eight endoscopists who were not informed of this study at all. These three endoscopists in turn attached the same resected lesion to a specimen board, measured the maximum resection diameter and tumor size, and recorded it. Therefore, the lesion was attached three times and recorded three times. The specimen attached by the third endoscopist was submitted for pathological examination. The third endoscopist's specimen became the pathology specimen.

The primary outcomes were the difference in the maximum resection diameter of the specimens and the recorded tumor size attached by the three randomly selected endoscopists.

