#### 8. Possibilities of disadvantage and risk of individual health due to this research and study

After conventional ESD by an ESD expert, each specimen is attached and removed from the board and handed to the next endoscopist in another room three times. Therefore, there is

no direct influence on the patient.

The specimen attached by the third endoscopist will be submitted for pathologic examination. Third endoscopist's specimen becomes the pathology specimen. Therefore, there is no possibility of disadvantage or risk to individual health.

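### The protocol does not say that mounting order is randomised or recorded, and its primary outcome is a raw difference among three serial mountings, so any tissue change with position counts as endoscopist difference

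*Protocol*

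**What the plan says.** Section 7 (Implementation plan) describes the random element: "Three endoscopists were randomly selected before every ESD by the envelope method from eight endoscopists". The mountings are serial and on one piece of tissue: "These three endoscopists in turn attached the same resected lesion to a specimen board". The section adds: "Therefore, the lesion was attached three times and recorded three times". Section 8 describes the handling: "each specimen is attached and removed from the board and handed to the next endoscopist in another room three times".

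The last place differs from the other two: "The specimen attached by the third endoscopist was submitted for pathological examination".

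The outcome in Section 7 is a plain difference among the three endoscopists: "The primary outcomes were the difference in the maximum resection diameter of the specimens and the recorded tumor size attached by the three randomly selected". Section 4 (Aim) gives the question this should answer: "whether the size differs depending on the endoscopist who attached the specimen".

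The protocol does not state how the three places are assigned, whether position or time since resection is noted with each reading, or how the specimen is kept between mountings. No endoscopist mounts the same specimen twice.

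**The concern.** The aim is about people, and the study title attributes the discrepancy to human error. The readings, however, come from three successive mountings of the same soft tissue. The second and third endoscopists receive a specimen that has already been pinned, unpinned and carried to another room. If it has stretched, shrunk or dried on the way, the three readings differ even when all three endoscopists work identically.

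Two consequences need to be kept apart.

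- **The raw within-specimen difference.** It contains the position effect however the order was chosen. Randomising the order does not remove it.
- **Comparison of endoscopists across specimens.** Random order protects this comparison. If order went with the endoscopist, drift would appear as a bias in the endoscopist effects.

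The opposite error is also possible. If old pinholes guide the next mounting, successive readings are pulled together and the differences are understated.

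**Working it through.** The protocol gives no sample size, SD, drift or effect size, so there is no stated figure to reproduce. What follows is illustration; every value of s, d and n is an assumption.

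**Inputs from the protocol.** Three of eight endoscopists per specimen, which gives C(8,3) = 56 possible trios and 8 × 7 × 6 = 336 ordered trios; three mountings and three readings per specimen; outcome = difference among the three (all Section 7).

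**Model.** Reading = specimen + deviation of that mounting (normal, SD s) + d × (position − 1), where d is the drift in mm per re-mounting. There is no systematic endoscopist effect.

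**Step 1: no noise.** With s = 0 the position terms are 0, d and 2d, so the range is 2d. Drifts of 0.5, 1 and 2 mm give apparent differences of 1, 2 and 4 mm with no human contribution.

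**Step 2: share of variance.** The position terms 0, d, 2d have sample variance d², so the expected within-specimen variance is s² + d² and the share due to position is d²/(s² + d²).

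**Step 3: mean range of three.** Without drift this is 3s/√π = 1.693s. With drift it was found by simulation and confirmed by numerical integration.

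| s (mm) | d (mm) | mean range (mm) | rise over d = 0 | share of variance from position |
|---|---|---|---|---|
| 1 | 0 | 1.69 | – | 0% |
| 1 | 0.5 | 1.90 | 12% | 20% |
| 1 | 1 | 2.45 | 45% | 50% |
| 1 | 2 | 4.10 | 142% | 80% |
| 2 | 0 | 3.39 | – | 0% |
| 2 | 0.5 | 3.49 | 3% | 6% |
| 2 | 1 | 3.80 | 12% | 20% |
| 2 | 2 | 4.90 | 45% | 50% |

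Only d/s matters for the percentage, which is why the s = 2 rows repeat the s = 1 rows at half the drift. At s = 3 mm and d = 0.5 mm the rise is 1.4%. These figures hold whether or not order is random.

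**Step 4: does order matter across specimens?** Simulation with 40 assumed specimens, s = 1 mm, eight endoscopists with no true difference, and an F test for endoscopist with specimen as block and no position term, at the 5% level (1,000 runs each):

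| d (mm) | random order | order fixed by endoscopist |
|---|---|---|
| 0 | 5.8% | 5.8% |
| 0.5 | 5.1% | 82% |
| 1 | 4.9% | 100% |

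In the same extreme case of a fixed order in all 56 trios, a 1 mm drift gives least-squares endoscopist effects from −1.31 to +1.31 mm, a spurious spread of 2.625 mm. This is the worst case; the protocol does not describe such an order.

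**Step 5: the opposite direction.** If successive deviations follow a first-order autoregression with correlation ρ, the expected within-specimen variance is the true one times 1 − (2ρ + ρ²)/3. For ρ = 0.3 that is 1 − 0.69/3 = 0.77, an SD ratio of 0.88 (12% too low). For ρ = 0.5 it is 1 − 1.25/3 = 0.583, a ratio of 0.76 (24% too low).

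**The case against.** **Silence is not non-randomisation.** A reader might infer that the order was not random. The protocol does not say so, and an envelope draw of three names may well have set the places too. This stands and limits the wording: order is unstated. It does not rescue the raw difference, because the figures in Step 3 are the same under random order.

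**Order by seniority or availability.** The special role of the third mounting makes this tempting, but nothing in the protocol supports it. Section 7 says the eight endoscopists knew nothing of the study, which counts against their choosing places. The 2.625 mm spread and the 82% and 100% error rates therefore show only why order should be fixed in writing.

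**Position and endoscopist can never be told apart.** This goes too far. They are inseparable within one specimen. Across specimens, with varying trios and random, recorded order, they can be separated.

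**The analysis plan may contain a position term.** It may, and its absence here is no finding. The point rests on what Section 7 itself governs: how places are assigned, what is recorded, and how the primary outcome is defined. A later model cannot use a position that was not recorded. Section 7 does at least make the third mounting identifiable.

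**The separate room prevents carry-over.** It may keep one endoscopist from seeing another's mounting. It does not undo physical change in the tissue or remove pinholes.

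**The effect may be negligible.** This stands. With large mounting noise and small drift the inflation is a few percent or less.

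**Conclusion.** The point holds as a weakness of design and outcome definition, not as a demonstrated bias. As Section 7 is written, any systematic change in the specimen from one mounting to the next is reported as a difference between endoscopists. If order also went with the endoscopist, the endoscopist effects themselves would be biased.

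The size is unknown. Over the assumed grid (drift 0.5 to 2 mm per mounting, SD 1 to 2 mm) the mean range is inflated by 3% to 142%, and anchoring on earlier pinholes would work the other way. Stretch, drying and pinhole effects are plausible for repeated pinning, but the protocol neither names nor measures them. Section 9 is concerned with accuracy at the level of several millimetres, so an artefact of 1 to 2 mm would matter to the interpretation if it occurred.

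**What to change.** In Section 7:

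- State that the envelope draws the order (first, second, third) as well as the three names.
- Require position and minutes since resection to be recorded with each reading.
- Define the reported result so that the position effect is shown separately from the endoscopist effect, with position as a fixed effect estimated across specimens. Only what remains after it should be attributed to endoscopists.
- State as a limitation that this removes average drift only. It does not correct for guidance by earlier pinholes or for change peculiar to one specimen.

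The cost is a sentence or two in Section 7, two extra boxes on the record sheet, and 2 degrees of freedom in the analysis. The one practical drawback is that scheduling must follow the drawn order.

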#### 8. Possibilities of disadvantage and risk of individual health due to this research and study

After conventional ESD by an ESD expert, each specimen is attached and removed from the board and handed to the next endoscopist in another room three times. Therefore, there is

no direct influence on the patient.

The specimen attached by the third endoscopist will be submitted for pathologic examination. Third endoscopist's specimen becomes the pathology specimen. Therefore, there is no possibility of disadvantage or risk to individual health.

#### 9. Medical contribution of this research and study

It is impossible to preoperatively evaluate the invasion depth, lymphovascular invasion, and vascular invasion of a lesion, but we cannot help but evaluate the presence or absence of lymph node metastasis based on lesion size. Because pathological examination including immunostaining is accurate, we endeavored to re-investigate the step in which error could occur. Because it is difficult to accurately measure the tumor diameter at the several-mm level with current endoscopic methods, the diameter is measured using an attached pathology specimen submitted as the post-resection specimen. More accurate pathological specimen sizing will be obtained.

#### 10. Protection of individual human right and informed consent during this research and study

Patients will be provided informed consent by verbal and written forms.

The ethical protection of individual human rights are conducted according to the Helsinki Declaration.

##### ① Protection of privacy and individual information.

All researchers in this study have to handle patient privacy and individual information sufficiently and protect it adequately.

Moreover, no researcher will be allowed to publish any data or information that might identify the patients.

##### ② Method of handling patient information and identification of researchers.

All patient names are encoded, and the correspondence table between the codes and patients is provided a safe management system in Ehime Rosai Hospital and Kagawa University Hospital.

All correspondence tables between codes and patients will have to be deleted and permanently disposed of.

#### 11. Other

Trial registration

University hospital Medical Information Network (No. 000012915)
